### Recruitment

To minimise risks of recruitment bias, recruitment of the participants will be done before randomising clusters [11]. An invitation to participate in the study will be sent to the supervisors of all units initially interested in joining the research. The email will include a link to study information and electronic informed consent with the Research Electronic Data Capture tool (REDCap) [40]. After a participant gives electronic informed consent, REDCap will lead them to a baseline survey (background information of the participants of the specific units, baseline data). After baseline data collection, unit leaders will be allocated to the study group as their unit.

All staff members who are working in the same unit as the participating unit leaders will be invited to join the study. First, staff members will receive a general invitation email, including a link to a site for baseline data collection, sent by the unit leader (for privacy reasons) to explain the purpose of the study and its practical arrangements. If the staff member is willing to join the study, they will give electronic consent (REDCap) and respond to the electronic surveys; but they do not join online training. Again, after providing baseline data, each staff member will be allocated to the same study group as their unit leader. The invitation email will include an explicit statement that participation is entirely voluntary, that non-participation will not have any consequences for staff, and that all responses will remain confidential. Participants will also be informed about the study’s purpose, procedures, and any potential risks or benefits. It is emphasised that staff members are not compelled to participate against their will or under pressure. Since the link to the data collection site that will be sent by the unit leader is general (non-specified with staff member’s name), the unit leaders will not be aware of who is joining the study or who is not. In addition, the study invitation will be framed as an opportunity for professional development or improvement rather than a requirement, making it less likely to be perceived as coercive.

To enhance recruitment and reach the target sample size, reminders will be sent via email to potential participants. If necessary, recruitment will be expanded to new locations and departments.

An overview of the trial profile is described in Fig. 2.

**Fig. 2 Fig2:**
[figure not shown]
Flow chart [14]

### Randomisation

Randomisation in this study will be conducted at the unit level (cluster), not at the hospital level. Units participating in the study will be randomly assigned (1:1) to one of two parallel groups: either the evidence-based leadership training group or the passive control group. This will be done using a computer-generated randomisation list developed by an independent trial statistician. To ensure balance between the study groups, units will be stratified based on the number of staff members in each unit as follows: (I) small units and (II) large units, determined by the median number of staff members in each unit. The randomisation will be generated using SAS software, Version 9.4 of the SAS System for Windows (SAS Institute Inc., Cary, NC, USA).

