**Methods:**

The effectiveness of the online training course will be evaluated using a cluster randomised two-arm controlled trial. Participants will be unit leaders recruited from hospitals in the Helsinki and Uusimaa Hospital District in Finland. At least 12 units will be represented, with approximately 25 participants in each unit (6 units in each arm). The sample for analysis will consist of at least 300 staff members. In the intervention arm, participants will be invited to join the online leadership course, while participants in the control group will continue practice as usual. The primary outcome is evidence-based practice, while the secondary outcomes are self-esteem, self-efficacy, implementation of EBP, quality of care, as well as work absence and intention to leave. The effectiveness of the intervention on the primary and secondary outcomes will be assessed based on the intention-to-treat principle. Feasibility data will be analysed separately. Sample size calculations are based on preliminary power analyses.

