#### Eligibility of the clusters and individual participants

For a cluster to be eligible for participation, it should comprise a unit providing specialised or primary care with at least 20 staff members (unit leaders and other staff) and be interested in joining the study. A ‘unit’ here refers to a ward, department, or any independent operational entity that has its own immediate leader or supervisor. Units will be excluded if they have low staff capacity (fewer than 20 total staff members), if they do not provide treatment to patients (e.g., supply management, laboratory), or if they are expected to undergo significant operational changes or closures.

The online training course is designed to target unit leaders working in the social or health care sector in a managerial position. Unit leaders were selected as the primary target group of the course because they represent important first-level actors in the implementation process of evidence-based knowledge into clinical practice [22]. To be eligible for participation, unit leaders should 1) have a professional licence to work in the health or social care sector, 2) have an official managerial position at the study organisation, 3) demonstrate a willingness to join the study, 4) represent any gender, 5) be able to speak, read, and write in Finnish, 6) and give (individual level) informed consent to join the study. Unit leaders with a background in nursing or medicine (doctor, dentist) should hold positions in strategic, middle, and supervisory management within social and healthcare units [23]. Unit leaders on long-term sick leave or study leave will be excluded.

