### Sample size

A previous study indicated a 6-point increase in the EBPQ outcome from baseline to a key time point in the intervention group and a 5-point decrease over time in the control group [35]. We assume there will be a 10-point difference in the change of the primary outcome over time between the two groups and an estimated standard deviation of 20 [36]. With a power of 80%, a 5% type I error with a two-sided test, an inter-class correlation (ICC) of 0.03, and an average unit size of 25 with a variation of 1, the estimated sample at the cluster level is 12, 6 in each treatment arm. This would mean a total of 300 participants, 150 in each arm. As in many other trials, we anticipate challenges in recruitment and adherence due to the limited time and resources of nurse staff, trial-specific issues, communication difficulties, inadequate research experience and training, and a lack of incentives [37]. We assume that if 58% of participants complete the post-intervention assessment after the online training [38], the number of staff to be recruited for the study should be 517. Generally, if the average response rate for the baseline is 42% [39], we should aim to approach at least 1,238 nursing staff. The potential number of participants needed for this study is feasible, as the data will be collected in the wide region in south Finland. The power calculation was made using PASS 15 software for a cluster randomised design.

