### Blinding and masking

The investigators who will enrol the units (clusters) will not be able to foresee the assignment. The allocation for each site will be kept blinded, and the staff of each unit will complete the baseline data collection before unit randomisation. When the training coordinator is ready to implement the training for the staff, the statistician will send the allocation groups by email directly to the training coordinator.

Due to the type of intervention, allocation results will be unmasked after randomisation to the unit leaders, contact persons for each unit, staff of the units, the training coordinator, and the researchers participating in the intervention design and implementation; this will reflect a real-world situation.

The leaders whose units are randomised to the intervention group will be registered on the Moodle platform by the training coordinator. Investigators running the preliminary analysis for the Data Management Committee (DMC) will be masked to data until investigators release the database. The statisticians will be masked to unit allocation in each arm.

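### Allocation is balanced on unit size alone and baseline EBPQ is not a named covariate, so chance imbalance between as few as 6 and 6 units is left larger than it need be

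*Protocol article*

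**What the plan says.** The Randomisation section gives the aim of stratifying as "To ensure balance between the study groups". It names one factor, staff number: "units will be stratified based on the number of staff members in each unit as follows: (I) small units and (II) large units". The two strata are "determined by the median number of staff members in each unit", and the section states no other restriction on the draw.

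The Sample size section plans few clusters: "the estimated sample at the cluster level is 12, 6 in each treatment arm". The abstract makes 12 a minimum.

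On timing, Blinding and masking says that "the staff of each unit will complete the baseline data collection before unit randomisation". Recruitment gives the same order, and the baseline survey carries the EBPQ.

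On the kind of unit, the eligibility section admits "a unit providing specialised or primary care with at least 20 staff members", and counts wards, departments and other independent entities as units.

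Under Data management and statistical analysis, the metric is change from baseline to month 7, analysed by a mixed model adjusted for participant and unit characteristics that are not listed there. The covariates named later in that section are age, gender, leader or staff status, and number of course tasks returned. Neither baseline EBPQ nor size stratum is among them.

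**The concern.** With 6 units against 6, one draw can leave the arms visibly different at baseline. Stratifying on size limits this only so far as size predicts the outcome. Baseline score usually predicts follow-up score well, and here it is in hand before the draw.

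A change score does not fully absorb a baseline imbalance. Units that start high by chance tend to fall back and units that start low tend to rise, so part of the imbalance passes into the difference in change unless baseline is also a covariate. At stake is how precise and how believable the primary contrast is in the one allocation that will be realised.

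**Working it through.** **The plan's own figure.** Inputs from Sample size: difference 10, SD 20, power 80%, two-sided 5%, ICC 0.03, mean unit size 25, variation 1 (read as coefficient of variation 1).

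- Individuals per arm without clustering: 2 × (20 × (1.960 + 0.842) / 10)² = 62.8.
- Design effect for equal units: 1 + 24 × 0.03 = 1.72. With L = 25 × 0.03 / 1.72 = 0.436, relative efficiency is 1 − L(1 − L) = 0.754, so the effective design effect is 1.72 / 0.754 = 2.28.
- 62.8 × 2.28 = 143.2 per arm, and 143.2 / 25 = 5.73, rounded up to 6. The 12 units reproduce. Nothing below changes that number.

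**Chance imbalance in baseline EBPQ.** Assumption: SD 20 and ICC 0.03, which the plan gives for its change-score calculation, also describe baseline scores. Equal unit sizes are used for simplicity.

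- Variance of a unit mean with m respondents: 400 × (0.03 + 0.97/m).
- SD of the arm difference: SD of a unit mean × √(2/6).
- m = 25 is the planned analysed size. m = 43 is the planned baseline recruitment, 517 / 12 = 43.1.

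| m | ICC | SD of unit mean | SD of arm difference | over 3 points | over 5 points |
|---|---|---|---|---|---|
| 25 | 0.03 | 5.25 | 3.03 | 32% | 10% |
| 43 | 0.03 | 4.59 | 2.65 | 26% | 6% |
| 25 | 0.10 | 7.38 | 4.26 | 48% | 24% |
| 43 | 0.10 | 6.96 | 4.02 | 45% | 21% |

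The ICC of 0.10 is an assumption that shows the range.

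**What reaches the result.** If follow-up regresses on baseline with slope b, an imbalance d shifts an unadjusted change contrast by (1 − b) × d in size. For b from 0.4 to 0.7 (assumption):

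- d = 3: 0.3 × 3 = 0.9 to 0.6 × 3 = 1.8 points.
- d = 5: 0.3 × 5 = 1.5 to 0.6 × 5 = 3.0 points.

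Against the planned 10 points, that is 9% to 18% and 15% to 30%.

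**Cost of adjustment.** Twelve units in two arms leave about 10 between-unit degrees of freedom. Size stratum takes one, leaving 9; a second unit-level covariate leaves 8. Respondent-level baseline EBPQ is estimated on about 300 people and takes almost none. At m = 25 and ICC 0.03, the unit-mean variance is 12.0 between units plus 15.5 from individual sampling, so 15.5 / 27.5 = 56% of it is individual variation.

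**What a restricted draw would gain.** With 6 small and 6 large units there are 20 × 20 = 400 allocations that put 3 of each in each arm. Simulation with m = 25 and ICC 0.03, keeping the best 80 (20%):

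- No further restriction: mean absolute imbalance about 2.4 points.
- Scored on unit mean EBPQ alone: about 0.4.
- Scored jointly, with equal weight, on EBPQ and number of primary-care units, with 4 such units falling 2 and 2 across the size strata (assumption): about 0.95.

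**The case against.** The strongest reply is that nothing here is an error. Size-stratified allocation of clusters is a recognised, valid method, the section is consistent with itself, and restricted randomisation is a refinement. That stands. A reader might infer that the treatment comparison is biased. It is not biased in expectation, and the shift worked out above is conditional on an imbalance that may not occur.

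Three more inferences are tempting and not supported:

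- *That imbalance on 12 units is beyond repair in the analysis.* The degrees-of-freedom count shows otherwise. Adjustment is cheap, and the plan already provides for some in general terms; a separate analysis plan may list baseline EBPQ. What remains is that the covariates this document does name omit it.
- *That a 5-point baseline difference amounts to half the planned effect.* The 10 points are a difference in change, and only the fraction 1 − slope of a baseline imbalance enters that contrast.
- *That primary and specialised units will probably be unevenly split, confounding deaths, complaints and absence.* Level of care can only be inferred from the eligibility rule, is not among the unit characteristics listed for collection, and its mix is unknown; the abstract speaks only of hospitals. There may be no primary-care units at all.

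It is also fair to say that 12 is a minimum, that baseline EBPQ is known for respondents only, and that loss to follow-up (58% completion is planned for) would weaken balance achieved on everyone measured at baseline.

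**Conclusion.** The point holds as a weakness of precision and credibility. The protocol restricts allocation on staff number only, has baseline EBPQ available before the draw, and names neither baseline EBPQ nor size stratum as a covariate for an outcome analysed as change.

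Under the planning SD and ICC carried over to baseline, a difference between arms of more than 3 points would arise in roughly a quarter to a third of draws, and of more than 5 points in 6% to 10%. Higher ICCs make both more frequent, and more units make them rarer. The consequence for an unadjusted contrast is modest but not negligible beside a 10-point target, and it rests on an assumed slope. The sample size is unaffected.

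**What to change.** 1. **Analysis, in any case.** State that the primary mixed model includes respondent-level baseline EBPQ and the size stratum as fixed covariates. This costs one between-unit degree of freedom and a sentence of text, and it applies even if the units have already been allocated.

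2. **Allocation, only if the draw has not been made.** Keep the two size strata. For 12 units, have the independent statistician list the 400 size-balanced allocations and score each on the arm difference in unit mean baseline EBPQ. If both types of unit are enrolled, score also the difference in number of primary-care units. Keep about the best 20%, check that no two units are always together or always apart, and draw one at random. Describe the procedure in the Randomisation section.

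The cost of the second step is a short program and two practical conditions. All units must be randomised in one draw, to which the median split already points because it needs the full list of units. Unit-mean baseline data must also reach the independent statistician beforehand, which needs a small change because the protocol limits data access to three named study roles. The Trial status section plans for recruitment to end on 31 October 2025, so the sponsor should first establish whether allocation has taken place.

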### Blinding and masking

The investigators who will enrol the units (clusters) will not be able to foresee the assignment. The allocation for each site will be kept blinded, and the staff of each unit will complete the baseline data collection before unit randomisation. When the training coordinator is ready to implement the training for the staff, the statistician will send the allocation groups by email directly to the training coordinator.

Due to the type of intervention, allocation results will be unmasked after randomisation to the unit leaders, contact persons for each unit, staff of the units, the training coordinator, and the researchers participating in the intervention design and implementation; this will reflect a real-world situation.

The leaders whose units are randomised to the intervention group will be registered on the Moodle platform by the training coordinator. Investigators running the preliminary analysis for the Data Management Committee (DMC) will be masked to data until investigators release the database. The statisticians will be masked to unit allocation in each arm.

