The online training intervention will be run in small groups with unit leaders (about 15 participants in each training group). Tutors (1/group) with an academic and/or healthcare professional background will follow participants’ and their team’s learning process in each small group. Tutors will receive centralised training on the study requirements through a total of 4 h of hands-on training sessions. These sessions will cover topics related to the tutor’s role, which includes carefully monitoring participants’ engagement (returned tasks and course drop-outs, peer discussions, and any other activity), answering practical questions related to the course via group chat and/or email, and giving feedback on all course assignments. Although no makeup sessions will be organised if a participant misses a training session, individual participants (or the tutor) may still request extended time to complete their tasks. However, a unit leader can choose to stop participating in the online course at any time, for any reason, without staff needing to withdraw from the entire study (i.e. the staff can still provide follow-up data). A student may be removed from the online course if, for example, they behave unethically towards other students. At the beginning of the course, the ethical guidelines regarding online education will be presented.

In line with the Finnish National Board on Research Integrity (TENK) guidelines [28], no compensation or reimbursement will be paid to the study participants. No additional support, training, or mentoring related to leadership skills will be offered by the research team after the intervention period.

Details of the assumptions and intervention mechanism, pedagogical approaches, learning process, structure, and content of the course are described in the intervention protocol [17]. In addition, the structure and content of the intervention are described in Additional File 2 using the GREET checklist [16].

No specific activities will be organised for the passive control group participants.

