Only study investigators, i.e. the Principal Investigator (MV), researcher (MS), and statistician (MY) will have access to the data. No interim analysis will be conducted. The results of the baseline data analysis will be shared and discussed with the DMC. If any significant external factors arise, such as nursing strikes, major organisational changes that alter the unit leaders’ roles, or severe resource shortages within the participating organisations that threaten the study’s implementation or participant recruitment, the trial may be terminated. The final decision to stop the trial will be made by the TSC based on the recommendations of the DMC.

Code breaks will occur only in exceptional circumstances, for example, if during the analysis, the statisticians detect any harm in the data scores. However, this will be done only after discussions with the TSC and based on recommendations of the DCM.

No adverse effects are anticipated due to the educational nature of the intervention. At the end of the intervention, all participants will be systematically asked about any perceived burden or harm caused by the intervention. If participants have perceived (ad-hoc or based on systematic assessment) any unintended effects or burden during or at the end of the intervention, they will be advised to seek care and support from the organisation’s occupational health services. All reports will be reviewed by the principal investigator and discussed during DMC meetings.

The specific criteria for stopping the study are as follows: [1] a significant decline in participant engagement or attendance (e.g. less than 20% course participation) may indicate that the intervention is no longer effective or relevant; [2] consistent negative feedback from participants regarding the content, format, or delivery of the intervention may warrant its cessation; [3] the educational intervention may not be financially sustainable due to unforeseen events (e.g. a catastrophe or staff strike); [4] changes in organisational policies, on-the-job training standards, or regulations may necessitate cessation; and [5] the introduction of a similar compulsory educational initiative or program that supersedes the current intervention may lead to its discontinuation.

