Data analysis will be carried out on an intent-to-treat (ITT) basis; every effort will be made to collect outcome data from all participants, regardless of whether they completed the intervention. Assumptions of normality of the residuals will be investigated. The characteristics of the units and respondents (staff members) will be summarised with descriptive statistics for each group. The specific metric will be the change between the baseline score and the final score at 7 months. The method of aggregation or the summary statistics will be based on the type of outcomes. Mean score will be used for score measurement such as the EBPQ, self-esteem, self-efficacy, and EBP scales. The Quality of care and Work absence and intention to leave will be summarised using both count and proportions.

All individuals within the cluster will be included in the trial. Possible duplicate measurements will be identified using participant ID codes, email addresses, or monitoring records.

A descriptive summary of the baseline information for both clusters and individuals will be presented first as tables of summary data. For the primary outcome EBPQ, its change from the baseline to the time immediately after the intervention (key time point) will be analysed with mixed effects linear models (respondents nested within units). In such models, the mean difference in EBPQ scores from baseline to the key point of intervention will be compared between the intervention and passive control groups, with random effects among unit leaders being estimated and characteristics of participants and units being adjusted. The changes in the subscales of the EBPQ will be analysed using multivariate mixed effects models in which simultaneous models for the three subscales are analysed jointly to overcome the inter-subscale correlation that might lead to multi-comparison bias [44]. Multiple imputations for the EBPQ and its subscales will be considered if data is missing at random. The same models will be used for the secondary outcomes, such as scores on the RSE, GSE, EBP and other continuous respondent-level outcomes. For unit-level outcomes at the key point, such as death, number of reported complaints, and number of staff’s sick days, generalised linear models will be used to compare the differences between the two groups with adjustment for unit characteristics.

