Sensitivity analyses will be conducted for units in which participation in online training is low to evaluate whether intervention fidelity has any effect on the results of the primary outcome. Results will be expressed using rate ratios, odds ratios, or least-squares mean differences with corresponding 95% CIs, depending on the type of outcome.

As our study will be a cluster randomised controlled trial, its analysis requires special consideration of the correlations within and between the clusters. First, in the sample size calculation, a clustering effect was assumed and accounted for as the ICC coefficient. Second, for the primary analysis, the intracluster (intraclass) correlation coefficient (ICC) will be reported as the proportion of the total variance of the outcome that can be explained by the variation between clusters [14]. For data analysis, the mixed effects model or two-level multilevel models that consider clustering effects will be used. In the model analysis, the variation in the outcomes among clusters will be estimated and tested for significance. Third, the overall efficacy of the outcomes will be estimated after considering the clustering effects.

In addition, covariate analysis will be conducted to control for potential confounding factors in statistical modelling. Participants’ age (novice, senior) and gender (male, female, other), status (unit leader, other staff member) and the engagement of course tasks (number of returned tasks by each participant in the intervention group) will be included in the analysis.

Statistical analyses will be performed with the SAS System for Windows, version 9.4 (SAS Institute Inc) and SPSS, versions 25.0 to 27.0 (IBM Corp). Because no adjustments for multiplicity of testing will be made, only 95% CIs will be reported for the secondary outcomes.

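### The statisticians' masking cannot last through all the planned analyses, because two of them use course data that arise only in the intervention arm

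*Protocol article*

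**What the plan says.** Two sections of the protocol article set the masking rule. Blinding and masking says "The statisticians will be masked to unit allocation in each arm" and gives no point at which this ends. Interim analyses and stopping rules adds: "Code breaks will occur only in exceptional circumstances, for example, if during the analysis, the statisticians detect any harm in the data scores". It makes any such break subject to discussion with the steering committee.

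Data management and statistical analysis sets two analyses that draw on the course. In the covariate analysis, listed with age, gender and status, "the engagement of course tasks (number of returned tasks by each participant in the intervention group) will be included in the analysis". For the primary outcome, "Sensitivity analyses will be conducted for units in which participation in online training is low".

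On the control arm, Interventions says "No specific activities will be organised for the passive control group participants". Blinding and masking has only the leaders of intervention units registered on the learning platform. It also unmasks the unit leaders, contact persons, unit staff, the training coordinator and the researchers involved in the intervention.

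On the allocation list, Randomisation has an independent trial statistician produce it. Blinding and masking then says "the statistician will send the allocation groups by email directly to the training coordinator".

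**The concern.** A variable that can be filled in only one arm identifies that arm to whoever holds it. The article promises that the statisticians do not know the allocation, and it also assigns them such a variable.

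This matters because the primary outcome, the EBPQ, is a self-report questionnaire answered by leaders and staff who know their allocation. Masking of the statisticians is the main protection against knowledge of allocation that the article claims after randomisation. (It also masks the investigators who run the preliminary analysis for the data committee, but to data.)

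Masking protects most where analysis decisions are still open, and as written some are. On missing data the article says "Multiple imputations for the EBPQ and its subscales will be considered if data is missing at random". The primary model adjusts for participant and unit characteristics that its own description does not list, and no threshold defines low participation. An analyst who knows the arms could settle such points, even unknowingly, in the direction of the hypothesis. A final report that described the statisticians as masked throughout would also be inaccurate.

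**Working it through.** The masking statement carries no figure, and the sample-size calculation has no bearing on it. The check is to set the rules side by side.

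**1. How long the masking is meant to last.** The masking sentence has no end point. The code-break rule gives as its example something the statisticians notice while analysing. That example makes sense only if they are still masked at that stage, so the masking is meant to cover the analysis itself.

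**2. Where the course data can exist.** Returned tasks are defined for participants in the intervention group. Controls have no course activities and are not registered on the platform. The field can therefore be filled only for intervention units and is empty or undefined for every control unit.

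**3. What the analyst can infer.** At the planned minimum of 12 units, 6 per arm, returned tasks can appear for at most 6 units and for no control unit. A unit with any returned task must be an intervention unit. If arms are coded A and B, one such unit shows which letter is the intervention. Reading every unit's allocation from the course data alone takes at least one record from each trained unit.

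**4. Which analyses are affected.**

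| Planned analysis | Course data needed? | Can it be run masked? |
|---|---|---|
| Primary mixed model for EBPQ change | None named | Yes, under coded arms, if course data are withheld |
| Covariate analysis with returned tasks | Yes, intervention arm only | No |
| Sensitivity analysis by training participation | Yes, intervention arm only | No |
| Feasibility and fidelity summaries | Yes | No, but the Abstract says feasibility data are analysed separately |

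The second and third rows conflict with masking through the analysis. The first does not, provided the order of data release is controlled. The article describes no such order.

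**The case against.** The strongest reply is that the conflict is narrow and manageable. Several parts of it stand.

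- The primary model does not name returned tasks. The covariate analysis is introduced as an addition, and the participation analysis is labelled a sensitivity analysis. Both could follow a masked primary analysis. A reader might infer that no analysis can be masked; the text does not support that.
- The Abstract says feasibility data are analysed separately, and the article never says that logins or course feedback reach the outcome analyst. A reader might count these as further sources of unmasking, but only returned tasks and training participation are expressly brought into the outcome analyses.
- A reader might infer from the allocation e-mail that the analyst holds the list. Randomisation calls the list-maker independent, and data access is limited to study investigators, one of them a statistician. Two different people is the more natural reading. The article does not state the separation, so this point is supporting only.
- Staff do not join the training, so course records come mainly from leaders, and a trained unit that never engages might leave none. Complete identification of units is not certain.
- Contamination and other-course answers are collected in both arms and do not reveal allocation in this way.
- A SAP that is not shown may fix the covariates, the imputation rule and the order of data release. Leaving those to a SAP is no fault in the article.

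None of this removes the conflict. Separate feasibility analysis does not take returned tasks off the covariate list or participation out of the sensitivity analysis. The point is not an omission: the article states a masking rule that covers the analysis, and it states analyses that break it.

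**Conclusion.** The point holds in a limited form. The statisticians cannot stay masked through all the planned analyses, because the returned-task and participation analyses reveal the arm labels once linked to unit codes. The primary EBPQ analysis can be masked, but nothing in the article secures this.

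The conclusion assumes that the masked statisticians also run the covariate and sensitivity analyses, and that the course data carry unit or participant codes that link to the outcome file. The article names no other analysts.

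The size of any bias cannot be derived from the document. A reader might take expected attrition as a measure: with 517 recruited and 300 analysed, 517 − 300 = 217 would lack month-7 data, and 217/517 = 42%. That shows how many participants the imputation decision could touch. It measures neither unmasking nor bias.

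No sample size, estimand or primary model changes. The masking statement should be corrected because it claims a property that the plan as written does not have.

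**What to change.** Amend Blinding and masking to state that:

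- The primary EBPQ analysis (covariates, missing-data decision and result) is completed and signed off under A/B arm codes by a statistician who does not hold the allocation list.
- Returned-task, login, participation and course-feedback data are kept in a separate file and released only after that sign-off.
- The engagement, fidelity and sensitivity analyses that use this file are described as unmasked.

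Contamination and other-course answers need not be withheld. The code-break paragraph should be aligned, so that the planned release of course data is not treated as an exceptional break.

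If this is not done, the masking claim should be limited to the analyses for which it can hold, or deleted.

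The cost is two data exports instead of one, a dated sign-off, and a slightly later start for the fidelity analyses. No new data and no recalculation are needed.
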